**Fig. 1 Fig1:**
[figure not shown]
Schedule of enrolment, interventions, and assessments according to the SPIRIT guidelines [40]. d day, w week, m month, Int intervention, MRI magnetic resonance imaging, mRS Modified Rankin Scale, NIHSS National Institutes of Health Stroke Scale, rIPostC Remote ischemic postconditioning, SSQoL Stroke-Specific Quality of Life, TOPICS-SF The Older Persons and Informal Caregivers Survey Short Form

### Sample size calculation

The sample size was estimated based on two trials [34, 35], which had a similar stroke population. Based on our clinical experience, we expect that a difference of 15 cm^3^ in infarct size between the two randomized groups should be considered as a clinically important difference. From the two trials, we estimated a standard deviation of 36 cm^3^. Based on α = 0.05 and power β = 0.80, we calculated that we need *n* = 90 per study arm. To account for an expected drop-out rate of 10%, we will include 100 patients in each group. This group size is comparable with other trials [20, 36] with the same intervention (rIPostC) and primary outcome (infarct size).

### Statistical analyses

Data will be analyzed according to an intention-to-treat analysis for all randomized patients. The primary outcome (infarct size) will be analyzed as a continuous variable using an independent *t*-test and presented with a 95% confidence interval for differences between both groups. Based on observations in previous research [2, 35, 37], we expect infarct size to be normally distributed. If the data are not normally distributed, a logarithmic transformation can be used. If this procedure fails, non-parametric alternatives will be used to analyze the data.

To analyze the mRS score, the odds ratio for a shift in the direction of a better outcome on the mRS will be assessed in both groups [38]. This ratio will be estimated with ordinal logistic regression and will be calculated for all possible cut-off values on the mRS.

For all continuous endpoints (e.g., quality of life, patient-reported outcomes, hospitalization, recurrent cerebrovascular accidents, and mortality, inflammatory, and vascular biomarkers), an independent *t*-test can be used to evaluate differences between usual care and rIPostC. We will consider the outcomes that are assessed at different time points (quality of life and patient-reported outcomes) as separate outcomes due to the possibility that there will be missing data after 12 months. If these continuous outcomes are, contrary to our expectations, not normally distributed, then a logarithmic transformation or non-parametric alternatives will be used.

Analyses will be done on the full data, and a sub-analysis will be performed excluding the patients who do not have a visible infarct on the MRI. Prior to analyses, the extent of missing data on all secondary outcomes will be evaluated and appropriate methods to handle missing data will be determined (e.g., multiple imputation). To ensure the analyses are blinded, all data will be blinded prior to analysis by an independent researcher. Full details of the analysis will be finalized in an analysis plan before the database is locked.

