### Patient population and randomization

Patients with an ischemic stroke who are being admitted to the emergency room of the Radboudumc are eligible for this study. Other inclusion criteria are: older than 18 years and a clinical diagnosis of an ischemic stroke (established by a neurologist, based on the World Health Organization criteria for stroke) [27]. Exclusion criteria include: unstable vital signs, admitted more than 12 hours after onset of symptoms, upper extremity injury, edema contra-indicating rIPostC, bilateral mastectomy, or axillary lymph node dissection. Patients with contra-indications for magnetic resonance imaging (MRI; e.g., those with a pacemaker, vascular clips, cochlear implants, or other implanted metal objects) will also be excluded because of the impossibility of assessing our primary outcome. All patients will provide written informed consent. For those patients who are not mentally capable of signing informed consent in the acute setting, oral assent will be obtained. This will allow the intervention to start while providing an opportunity for informed consent to be given when the patients or their caregivers are capable of making a well-considered decision. Patients who receive a change in diagnosis after inclusion will be excluded from the analysis of our primary outcome (infarct size).

After informed consent or oral assent has been given, randomization will be performed using a predefined table generated by the computer program SealedEnvelope. Patients will be randomized in a 1:1 ratio to rIPostC or sham conditioning by the coordinating investigator. Stratification will be performed for treatment received (thrombectomy, thrombolysis, or no revascularization treatment) to ensure equal allocation of these subgroups to rIPostC and sham conditioning.

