### Secondary outcome measures

(1) The validated and frequently used Modified Rankin Scale (mRS) [2, 28, 29] will be used to assess clinical outcomes after 12 weeks. To assess clinical outcomes at the end of hospitalization, the validated National Institutes of Health Stroke Scale [30] will be used. Both scores are calculated as standard after a stroke and will be assessed by a clinical physician or nurse from the neurology department.

After 12 months, we will also examine hospitalization, recurrent (cerebro)vascular events, and mortality. These data will be extracted from patient files at the Radboudumc.

(2) To assess quality of life, participants will be asked to fill out two questionnaires after 12 weeks and 1 year. The first questionnaire is the Stroke-Specific Quality of Life Scale (SSQoL), which is reliable and reproducible for self-reported quality of life outcomes in stroke patients [31]. The second questionnaire is the TOPICS-SF (The Older Persons and Informal Caregivers Survey Short Form), which is used for assessing patient-reported outcome measures. The TOPICS-SF has been shown to be a valid and feasible questionnaire for older patients [32, 33].

(3) Venous blood will be sampled during the first presentation at the emergency department and at the end of hospitalization to explore the impact of daily rIPostC on vascular, immune, and anti-inflammatory pathways. Whole blood will be spun down and serum will be stored at −80 °C for future analysis. For further analysis of possible underlying mechanisms, urine will also be sampled and stored at −80 °C at the end of hospitalization.

An overview of all outcomes and corresponding measurements is presented in Fig. 1.

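### The primary t-test ignores the revascularisation strata used at randomisation; if those strata predict infarct size, it is valid but conservative and gives up precision

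*Protocol article*

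**What the plan says.** Under Patient population and randomization, the protocol article sets out a stratified 1:1 scheme: "Patients will be randomized in a 1:1 ratio to rIPostC or sham conditioning", and "Stratification will be performed for treatment received (thrombectomy, thrombolysis, or no revascularization treatment) to ensure equal allocation of these subgroups". The schedule comes from a predefined computer-generated table; the article does not say how that table balances arms within a stratum.

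Under Statistical analyses, the primary test is named: "The primary outcome (infarct size) will be analyzed as a continuous variable using an independent" t-test, "presented with a 95% confidence interval for differences between both groups". If the data are not normal, a log transformation may be used, and then: "If this procedure fails, non-parametric alternatives will be used to analyze the data". Neither the test nor its fallbacks carries a stratum term. The section leaves full details to an analysis plan to be settled before database lock.

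Under Sample size calculation, the trial is sized for an unadjusted comparison of two means with an SD of 36 cm3: "we expect that a difference of 15" cm3 matters clinically, "Based on α = 0.05 and power β = 0.80", 90 per arm, raised to 100 for 10% drop-out.

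**The concern.** An analysis should normally reflect the factors on which randomisation was stratified. When arms are balanced within strata, differences between strata cancel out of the comparison of arm means. An independent t-test does not know this: its standard error uses the total variance, including the part that lies between strata. If the strata are prognostic, the reported standard error is therefore larger than the true one. The interval then covers more often than 95%, the type I error falls below 5%, and the test has less power than a stratum-adjusted analysis of the same patients.

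This is not merely a detail left to the later analysis plan. The article has already named the primary test, and an independent t-test has no place for a stratum term. What is at stake is precision in the trial's main result, not its validity.

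**Working it through.** **Inputs from the protocol article.** Difference 15 cm3, SD 36 cm3, alpha 0.05, power 0.80, 90 evaluable per arm (Sample size calculation); three strata and 1:1 allocation (Patient population and randomization).

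**Input not in the document.** R2, the share of infarct-size variance explained by the three strata. No stratum means or sizes are given, so R2 is assumed and shown from 0 to 20%.

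**Step 1: the plan's own figure.** n per arm = 2 × 36² × (1.960 + 0.842)² / 15² = 90.4, so 91 after rounding up, against 90 stated. A one-sided alpha would give 72, so the calculation is two-sided. Drop-out: 90 / 0.90 = 100, as stated. The stated size reproduces to within one patient per arm.

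**Step 2: the unadjusted test as planned.** Standard error = 36 × sqrt(2/90) = 5.367 cm3. Interval half-width = 1.96 × 5.367 = 10.52 cm3. Standardised effect = 15 / 5.367 = 2.795. Power = Phi(2.795 − 1.960) = 79.8%.

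**Step 3: allow for strata balanced by design.** The true standard error of the difference is 5.367 × sqrt(1−R2), while the t-test still reports about 5.367. Hence:

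- interval too wide by the factor 1/sqrt(1−R2)
- type I error of the t-test = 2 × [1 − Phi(1.960/sqrt(1−R2))]
- power of the t-test = Phi((2.795 − 1.960)/sqrt(1−R2))
- power of the stratum-adjusted test = Phi(2.795/sqrt(1−R2) − 1.960)

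For R2 = 20%, sqrt(1−R2) = 0.894. Type I error = 2 × [1 − Phi(2.191)] = 2.8%. Power of the t-test = Phi(0.934) = 82.5%. Adjusted power = Phi(1.165) = 87.8%.

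| Assumed R2 | t-test interval too wide by | Adjusted half-width (cm3) | t-test type I error | t-test power | Adjusted power | n per arm for 80% power, adjusted |
|---|---|---|---|---|---|---|
| 0 | 0 | 10.52 | 5.0% | 79.8% | 79.8% | 91 |
| 5% | 2.6% | 10.25 | 4.4% | 80.4% | 81.8% | 86 |
| 10% | 5.4% | 9.98 | 3.9% | 81.1% | 83.8% | 82 |
| 20% | 11.8% | 9.41 | 2.8% | 82.5% | 87.8% | 73 |

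**Step 4: check by simulation.** 180 patients, exact balance within three strata of assumed shares 20/30/50%, normal errors, 20,000 runs per setting. At R2 = 20% the t-test had type I error 3.0%, coverage 97.1% and power 81.7%, against 87.4% adjusted. At R2 = 10% it had type I error 4.2% and power 80.7%, against 83.4%. At R2 = 0 the two analyses performed alike (79.3% and 79.2%).

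**The case against.** The strongest reply is that the plan is consistent with itself. The trial was sized on the unadjusted SD and will be analysed by the unadjusted test, and at every R2 in the table that test has at least 79.8% power. It is valid, and its estimate is unbiased. This stands: what is forgone is power above the target, and a type I error below 5% is not a false-positive risk. A reader might infer that the trial is underpowered or its primary test invalid; the figures support neither.

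Second, the loss is conditional. The only reason given for stratifying is equal allocation. A reader might infer that the strata were chosen because infarct size differs between them, but the article does not say so and gives no data on it. The type I error and over-coverage figures also need balance within strata, for example by blocks, which the article does not describe, although balance is its stated purpose. Both limits stand, and they are why the size is given as a range starting at zero.

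Third, a reader might want to go further and adjust for admission NIHSS as well. The article specifies NIHSS at the end of hospitalisation. Its remark "Both scores are calculated as standard after a stroke" refers to that score and the 12-week mRS, so it does not show that a baseline score is collected. Nor is NIHSS a stratification factor: variance that it alone explains is not balanced by the design, does not make the t-test conservative, and cannot be put into the formulas for the t-test's type I error and power.

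Fourth, a reader might extend the point to the ordinal mRS model. The article names the model and says nothing for or against covariates, which is ordinary content for the later analysis plan. An adjusted ordinal odds ratio is also a different quantity from an unadjusted one, so the change would not be neutral there.

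**Conclusion.** The point holds as a conditional matter of efficiency and consistency in the primary analysis. The design stratifies on a three-level factor that the named primary test ignores. Over an assumed R2 of 5% to 20%, the interval is 2.6% to 11.8% too wide, and about 1.4 to 5.3 points of power are forgone (81.8 − 80.4 and 87.8 − 82.5). With R2 = 0 nothing is lost. These sizes rest on R2, which the document does not give, on balance within strata, and on the plan's own 15 cm3, 36 cm3 and 90 per arm. The planned 80% power and the validity of the test are not in question. The change is worth making because the strata must already be known in order to randomise, and the analysis plan is still open.

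**What to change.** State in the analysis plan, before database lock, that the primary analysis is a linear model of infarct size (log-transformed if needed) on arm plus the three-level revascularisation stratum used at randomisation, reporting the adjusted difference with its 95% confidence interval. Name a stratified rank test (van Elteren) as the non-parametric fallback, so that the fallback respects the strata too. Keep the independent t-test as a supportive unadjusted result.

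The cost is a sentence or two and two degrees of freedom (176 residual instead of 178 with 180 evaluable patients). That is negligible even if the strata turn out not to be prognostic. The sample size stays as planned, and no new data are needed.

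### Mortality and recurrent events (and hospitalisation, unless it means days) are classed as continuous, normally distributed endpoints for a t-test

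*Protocol article*

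**What the plan says.** The Secondary outcome measures section introduces three follow-up outcomes: "After 12 months, we will also examine hospitalization, recurrent (cerebro)vascular events, and mortality". Of their source it says "These data will be extracted from patient files at the Radboudumc". It does not say whether hospitalisation means any admission, a number of admissions or days in hospital.

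The Statistical analyses section then groups the same outcomes with questionnaires and biomarkers: "For all continuous endpoints (e.g., quality of life, patient-reported outcomes, hospitalization, recurrent cerebrovascular accidents, and mortality, inflammatory, and vascular biomarkers". For this group "an independent *t*-test can be used to evaluate differences between usual care and rIPostC". It says non-normality would go against what the authors expect, and that if these outcomes are "not normally distributed, then a logarithmic transformation or non-parametric alternatives will be used".

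The only categorical method named is for the mRS: "This ratio will be estimated with ordinal logistic regression and will be calculated for all possible cut-off values on the mRS". No binary, count or time-to-event method is named for the three event outcomes. The section closes by deferring detail: "Full details of the analysis will be finalized in an analysis plan before the database is locked".

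**The concern.** Whether a patient has died, or has had another stroke, by 12 months is a yes/no fact, or a time to an event if dates are kept. It is not a continuous measurement, and an expectation of normality has no meaning for it. The article nevertheless gives these outcomes a data type, a distributional expectation, a test and a fallback, all built for measurements such as a quality-of-life score.

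This is a wrong statement, not detail left for later. An analysis plan that follows the text inherits the misclassification, and one that departs from it contradicts the published protocol. At stake is how the clinical event outcomes are reported: whether readers get risks with an interval, and whether patients with less than 12 months of information are handled properly.

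**Working it through.** **The plan's own figure.** The article computes no figure for the event outcomes. Its only calculation is the sample size, used here just for the number per arm. With a difference of 15 cm³, SD 36 cm³, two-sided α 0.05 and power 0.80 (Sample size calculation section), n = 2 × (1.960 + 0.842)² × 36² / 15² = 2 × 7.85 × 5.76 ≈ 90.4, so 91 per arm against the stated 90. Power at 90 is 0.798. Allowing 10% drop-out, 90 / 0.90 = 100. The figure reproduces to within rounding, and the point does not depend on it.

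**Event rates.** The article gives none. Rates of 2% to 20% are assumed below.

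**1. Can the outcome be normal?** A 0/1 variable with event probability p has skewness (1 − 2p) / √(p(1 − p)), where a normal variable has 0.
- p = 0.02: 0.96 / 0.140 = 6.9
- p = 0.05: 0.90 / 0.218 = 4.1
- p = 0.10: 0.80 / 0.300 = 2.7
- p = 0.20: 0.60 / 0.400 = 1.5

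The stated expectation fails at every rate, so the plan's fallback is always in play.

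**2. What does the plain t-test do?** Exact type I error, summing binomial probabilities over all pairs of event counts with 100 per arm and complete data:
- 2%: 0.040
- 5%: 0.044
- 10%: 0.052
- 20%: 0.051

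The difference in means of 0/1 data is the risk difference. Coverage of its pooled-t interval, by the same method, lies between 93.7% and 95.5% for five assumed pairs of rates between 2% and 15%. On complete data the t-test is roughly serviceable.

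**3. What does the log option do?** log(0) is undefined, so plain logging fails for every event-free patient (80% to 98% of patients at the assumed rates). log(x + 1) maps 0 to 0 and 1 to 0.693. That is a change of scale, which leaves t unchanged and cannot reduce skewness.

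A simulated example has 8/100 events in one arm and 17/100 in the other:
- Pooled variance = (100 × 0.08 × 0.92 + 100 × 0.17 × 0.83) / 198 = 21.47 / 198 = 0.1084.
- t = −0.09 / √(0.1084 × 2/100) = −0.09 / 0.0466 = −1.93, p = 0.0547.
- After log(x + 1): t = −1.93, p = 0.0547.

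**4. What does the rank option do?** On the same data the rank-sum test gives p = 0.0549 and the uncorrected chi-square test p = 0.0543, so the p-value is usable. The effect measures that go with a rank test are not. The probability index is 4550 / 10000 = 0.455, which is only 0.5 − 0.09/2. The Hodges–Lehmann shift is 0, because 0.08 × 0.17 + 0.92 × 0.83 = 0.777 of all between-arm pairs are tied. Neither conveys 8% against 17%.

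**5. Follow-up.** The t-test, its log version and the rank test each need one complete value per patient at 12 months. None has a place for a patient whose information stops earlier.

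**The case against.** Several arguments on the other side have force.

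- **The fallback is a choice.** It offers non-parametric methods beside the log. A reader might infer that most patients would be lost to log(0). The text does not support that: it happens only if the analyst picks the one unworkable branch.
- **The t-test is not badly wrong on complete data.** A reader might infer inflated false positives, or that no risk estimate could be reported. Neither follows. Type I error is near nominal, and a difference in 0/1 means is a risk difference.
- **Early deaths.** A reader might infer that patients who die early are coded as free of recurrence, so that the arm with more deaths looks better. The article states no such coding rule and gives no death or recurrence rate. The size is also modest: if 10% of those at risk recur, 5 immediate deaths per 100 change the proportion from 10% to 95 × 0.10 / 100 = 9.5%. Cumulative incidence with death as a competing event would not remove this, because with complete follow-up it equals the crude proportion. That is why recurrence needs to be read alongside mortality.
- **Missing data.** The article says that the extent of missing data on secondary outcomes will be assessed and a method then chosen. It is not silent on loss to follow-up, although the named tests do not accommodate it.
- **Hospitalisation.** As days in hospital it would be quantitative, and a t-test, log or rank analysis would be ordinary. The point is firm for mortality and recurrent events only.
- **Permissive wording and deferral.** The t-test is offered, not required, and a later plan is promised. The absence of time-to-event detail from a condensed article is therefore no fault. The deferral does not cover a data type that has been stated wrongly.

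What stands is the misclassification and the mismatched rule attached to it.

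**Conclusion.** The point holds at moderate severity. The Statistical analyses section wrongly treats mortality and recurrent cerebrovascular accidents as continuous and normally distributed, and does the same for hospitalisation unless that means days. The log option cannot work for event data, the rank option yields no suitable estimate, and no named test deals with incomplete 12-month follow-up.

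The harm is limited. With complete data, the t-test's type I error of 0.040 to 0.052 is acceptable. This rests on 100 patients per arm and assumed event rates of 2% to 20%, since the article supplies none. Only secondary outcomes are affected, and the infarct-size analysis and sample size are untouched. The documents do not show that event dates or censoring information will be available, so time-to-event methods are conditional on that.

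**What to change.** In the protocol wording, or at the latest in the analysis plan promised before database lock:

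- Remove mortality and recurrent events from the list of continuous endpoints, and drop the normality expectation and log rule for them.
- Compare 12-month risks between arms with a risk difference or risk ratio and 95% CI.
- If event dates and censoring can be obtained from the patient files, use Kaplan–Meier and Cox for mortality instead. For recurrence, use cumulative incidence with death as a competing event, reported alongside mortality.
- Define hospitalisation as yes/no, a count or days, and choose the method to match. The existing t-test, log or rank rule can stay only if it means days.

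The cost is a small amount of wording and analysis work, with no extra patients or visits. Collecting event dates would add some extraction effort if it is not already planned.

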A potential approach may be the application of remote ischemic postconditioning (rIPostC). Remote ischemic conditioning (RIC) consists of several cycles of brief periods (5 min) of limb ischemia followed by reperfusion, which can be applied by inflating a simple blood pressure cuff. This intervention subsequently confers protection against severe ischemia in remote organs in humans [10–12]. Due to the unpredictability of stroke, applying RIC before the event is not possible. However, similar protective effects are present when RIC is applied during or even after an ischemic insult [13], which is known as rIPostC. Whilst the majority of studies have focused on the protective effects of ischemic pre- and postconditioning on cardiac tissue [10–12, 14, 15], recently, several studies have supported the ability of rIPostC to reduce neural damage after reperfusion [8, 16–19], validating that rIPostC may have clinical potential for stroke patients, with clinical trials showing promising results [20, 21]. Additionally, Hess et al. postulated that, in addition to the short-lasting benefits of a single bout of conditioning, chronic benefits may be induced with repeated daily conditioning [18]. This has since been supported by preclinical studies in mice and rats [22, 23] and further supported by evidence from clinical trials in humans with favorable clinical outcomes for repeated rIPostC in ischemic stroke patients [24, 25].

We, therefore, hypothesized that rIPostC during the first few days following an ischemic stroke reduces infarct size. Since infarct size is strongly related to functional recovery [26], repeated rIPostC may be a simple and novel strategy to minimize the clinical impact of an ischemic stroke. Importantly, rIPostC is virtually cost-free, non-pharmacological, and non-invasive, and it can easily be added to the current treatment of stroke patients.

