### Intervention: repeated remote ischemic postconditioning

A manual blood pressure cuff will be placed around the upper arm after the diagnosis of an ischemic stroke. All participants will receive four cycles of 5-min inflation of the blood pressure cuff, followed by 5 minutes of reperfusion. This procedure will be performed twice daily (morning and afternoon) during the hospitalization after the ischemic stroke for a maximum of 4 days. The level of cuff inflation differs between the groups. Cuff inflation in the rIPostC-group is >20 mmHg above systolic blood pressure, mediating full blockage of the arterial inflow. Subjects in the control group receive cuff inflation to 50 mmHg, which will not induce any ischemia. The intervention will be administered by a trained researcher. Blood pressure will be recorded before the intervention.

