### Primary outcome measure

The primary outcome measure will be the infarct size on day 4 after admission (or at discharge if discharge is before day 4), which will be compared between the intervention and control groups. The infarct size will be evaluated by diffusion-weighted MRI brain imaging using a 1.5-tesla MRI scanner (Siemens® Avanto). The infarct size will be annotated manually and analyzed on a dedicated work station by a trained researcher under the supervision of a neuroradiologist.

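### The visible-infarct sub-analysis selects patients on the primary outcome after randomisation, so it can understate, erase or reverse a real effect

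*Protocol article*

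**What the plan says.** All references are to the Protocol article.

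- **Statistical analyses.** The main rule is: "Data will be analyzed according to an intention-to-treat analysis for all randomized patients". Analyses use the full data, and in addition "a sub-analysis will be performed excluding the patients who do not have a visible infarct on the MRI". The sub-analysis is a commitment. No reason, exploratory label or limit on its interpretation is given. Full analysis details are left to an analysis plan due before database lock.
- **Primary outcome measure.** "The primary outcome measure will be the infarct size on day 4 after admission", or at discharge if that comes sooner. On the instrument: "The infarct size will be evaluated by diffusion-weighted MRI brain imaging using a 1.5-tesla MRI scanner". The text describes no other MRI.
- **Intervention.** Treatment is given twice daily "during the hospitalization after the ischemic stroke for a maximum of 4 days", so the scan follows randomised treatment.
- **Patient population and randomization.** Entry rests on a neurologist's clinical diagnosis; no infarct on a baseline MRI is required. Patients whose diagnosis changes after inclusion are already left out of the infarct-size analysis.
- **Background.** The hypothesis is that "rIPostC during the first few days following an ischemic stroke reduces infarct size".

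**The concern.** Having no visible infarct on the outcome scan is not a baseline characteristic. It is an infarct size of zero, the best value the primary outcome can take, and it is observed after treatment. The hypothesis is that treatment makes infarcts smaller, so treatment may itself move patients with small infarcts into the excluded group. Their sham counterparts, with small but visible infarcts, would stay in. What remains is a comparison of two groups selected differently by arm.

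At stake is how the result is read. A reader could take the visible-only contrast as the effect in patients with an established infarct, and could wrongly discount a positive full-data result if that contrast were null.

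**Working it through.** Differences are sham minus rIPostC, so a positive value favours rIPostC.

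**Inputs from the Sample size calculation section:** difference 15 cm3, SD 36 cm3, α = 0.05, power 0.80, 90 per arm, 100 after 10% drop-out.

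**Plan's own figure.** 2 × (36 × (1.960 + 0.842) / 15)² = 90.4, which agrees with the stated 90 (91 if rounded up). 90 / 0.9 = 100. Power at 90 per arm is 79.8%. The planned effect and SD are therefore used as the reference.

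**Not in the documents:** mean infarct size, its distribution, and the share without a visible infarct in either arm. All values below for these are assumptions.

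**1. Identity.** Let p be the share without a visible infarct and μ the mean among visible infarcts (c = sham, t = rIPostC). Then

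full-data difference = (1 − p_c) μ_c − (1 − p_t) μ_t.

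Assume μ_c = 40 cm3 and p_c = 10%, so the sham full-data mean is 0.9 × 40 = 36. Hold the full-data difference at 15, so that μ_t = (36 − 15) / (1 − p_t):

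| p_t | μ_t (cm3) | Visible-only difference (cm3) |
|---|---|---|
| 10% | 23.3 | 16.7 |
| 20% | 26.2 | 13.8 |
| 30% | 30.0 | 10.0 |
| 40% | 35.0 | 5.0 |
| 47.5% | 40.0 | 0.0 |

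The same 15 cm3 effect appears as anything from 16.7 to 0. Erasure needs a gap of 47.5 − 10 = 37.5 points. In 3,000 simulated trials of the last row (gamma sizes, SD 36, 90 per arm, two-sided t-test), the full-data difference was 14.9 cm3 with 83% power. The visible-only difference was 0.0, with 4.6% rejection.

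**2. Exponential sizes, fixed subtraction.** Assume a sham mean and SD of 36 cm3, with treatment removing d from each infarct, floored at zero. The full-data difference is 36 × (1 − exp(−d/36)). Setting this to 15 gives d = 19.4. The share of treated patients at zero is 1 − exp(−19.4/36) = 42%, against 0% of sham. Because the exponential is memoryless, the visible-only mean is 36 in both arms and the difference is 0. With d = 10, the full-data difference is 8.7 cm3, 24% of treated patients are at zero, and the visible-only difference is again 0.

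**3. Exponential sizes, proportional shrinkage.** Let treatment reduce the mean from 36 to 21 cm3, again a 15 cm3 effect. At any visibility threshold v, the visible-only means are 36 + v and 21 + v. The difference stays at 15, with no loss.

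**4. Gamma sizes, 20 cm3 subtracted, floored at zero.** Assume 10% in each arm have no infarct before treatment, and SD 36 (2,000 trials per row):

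| Assumed mean (cm3) | rIPostC without visible infarct | Full-data difference (rejection) | Visible-only difference (rejection) |
|---|---|---|---|
| 30 | 58.7% | 12.0 (68%) | −6.4 (15%) |
| 40 | 41.9% | 14.8 (83%) | 3.5 (9%) |
| 50 | 27.9% | 16.7 (88%) | 10.8 (44%) |

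**5. If treatment does not change the visible share.** Only sample size is lost. For a 15 cm3 difference among those remaining, excluding 10%, 20% or 30% (81, 72 or 63 per arm) gives power of 76%, 71% or 65%.

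**The case against.** **The size comes from the model.** The exact zero in step 2 follows from combining a memoryless distribution with a fixed subtraction, and it implies 42% against 0% without a visible infarct. Nothing in the documents suggests a gap that large. Step 3 keeps the same distribution and loses nothing. This stands, and only a range can be given.

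**A stronger reading is tempting:** that the sub-analysis is biased towards no effect or harm whenever the treatment works. The documents do not support it. Treatment may work by shrinking infarcts that stay visible, and then there is little or no such bias.

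**The primary inference is protected.** The restricted analysis is additional and no decision rule hangs on it. A reader might infer that the trial's main result is compromised; it is not. That the sub-analysis would be read as the effect in true strokes is a prediction, not something the article says.

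**It may be meant to remove stroke mimics.** Entry is clinical, so this is an understandable aim, but it is weak as a defence. Patients with a changed diagnosis are already excluded from the infarct-size analysis. Those who remain still carry a stroke diagnosis, and for them zero is a valid result.

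**Some material is not visible.** The later analysis plan may label the comparison, and Fig. 1 is not shown, so a baseline MRI cannot be strictly ruled out. But the article already commits to the rule, and its text describes only the outcome scan.

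**Conclusion.** The point holds in conditional form. As written, the sub-analysis selects on the best value of the primary outcome, measured after randomised treatment, so its two groups are not protected by randomisation. Whether that produces bias, and how much, depends on how far treatment changes the share with a visible infarct.

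For a full-data effect of about 15 cm3, the assumed models give visible-only differences from 15 to 17 cm3 (proportional shrinkage, or share unchanged) down to 0 (37.5 to 42 points more treated patients without a visible infarct). A reversed sign appeared in one assumed case, with a full-data effect of 12.0 cm3 and a gap of about 49 points. These are illustrations of what can happen, not estimates for this trial. The conclusion also assumes that the MRI named in the rule is the outcome scan. The consequence is moderate, because the full-data comparison is untouched.

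**What to change.** Do not use the visible-only comparison as evidence of a treatment effect. Either replace it, or keep it labelled as exploratory and non-randomised; dropping it outright is not required. In both cases:

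- report the proportion with a visible infarct by arm, as a risk difference with 95% CI, beside the full-data volume comparison;
- state that zero is a valid infarct size and stays in the full-data analysis;
- define any confirmed-stroke subgroup only from information available before randomisation. The text describes no baseline MRI, so such information may not exist, in which case the subgroup should not be formed.

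The cost is wording in the analysis plan that the article says will be finalised before database lock. The proportion comes from scans already planned, so no new data or patients are needed.
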